## Abstract

**Background:**

Low back pain (LBP) is a ubiquitous, heterogeneous disorder that affects most people at some point in their lives. The efficient management of LBP remains elusive, with direct and indirect costs attributed to LBP surpassing many other common conditions. An emphasis on a structural basis of LBP often fails to recognize movement, specifically patterns of movement that may provide biomechanical signatures of painful conditions. The primary objective of this registry is to understand the differences in movement patterns among those with LBP and those without pain in a U.S. population sample.

**Methods:**

This ongoing, non-randomized, prospective post-market registry will consist of two groups: patients with LBP, and age and sex-matched controls without LBP. We will seek to recruit 132 subjects in each group. Data collection will take place in two phases: (1) baseline assessment of LBP patients and matched controls; (2) assessment of LBP patients at 6 and 12-months follow up. The primary outcome measure will be differences in movement patterns between those with LBP and those without LBP. Secondary outcomes will include differences in patient reported outcomes including pain, disability and quality of life.

**Discussion:**

The findings will help determine if there are meaningful differences in movement patterns between those with and those without LBP. Further, an initial understanding of movement signatures specific to certain subtypes of patients with LBP may be achieved.

**Trial registration:**

The study was registered on the clinicaltrials.gov portal: NCT03001037. Trial retrospectively registered 12/22/2016.

## Background

Low back pain (LBP) represents a complex constellation of conditions that commonly afflicts the adult population. As the main contributor to years lived with disability [1], it is an enormous public health issue, with associated expenditures being three times greater than diabetes, cancer and heart disease [2]. Despite these costs, the treatment and prognosis for persistent LBP remain quite poor. Unfortunately, symptomatic mismanagement of LBP likely represents an underlying lack of understanding of the multifactorial contributions to the condition. Importantly, dynamic real-time understanding of movement patterns and biomechanics have historically been rudimentary and are often dependent upon the skill and expertise of the examiner. Moreover, assessments of these key factors frequently rely on the “eyes” of the clinician and the subjective feedback of the patient.

A systematic review and meta-analysis of studies comparing lumbo-pelvic kinematics in people with and without back pain demonstrated significant limitations in the included studies, specifically a lack of detail or standardization between studies on the criteria used to define participants as those with LBP or without LBP [3]. Furthermore, the reliability of the most common means of measuring lumbar sagittal motion (plurimeter V double inclinometer, the carpenter double inclinometer and the computerized single sensor inclinometer) was found to be greatly varied, falling below clinically desirable levels with errors primarily attributed to the examiner [4]. Using 3D lab-based motion analysis, Hemming et al. [5] evaluated spinal kinematics between healthy individuals and subjects with chronic low-back pain. They observed significant differences in lower-thoracic and upper-lumbar movement during functional tasks in a UK-based population. However, they specified a lack of analysis of muscle activity as a limitation to better understand underlying pain mechanisms. Moreover, they noted that use of continuous postural measurement devices may improve understanding around movement-related behavior, and behavioral change [5].

Recent technological advances offer new opportunities for accurate, convenient measurement of movement and posture as correlated to pain, thus theoretically allowing a more in-depth understanding of the foundations of chronic LBP. Laird et al. [6] utilized wireless, wearable, sensor technology (ViMove; dorsaVi Ltd., AUS) to evaluate lumbo-pelvic kinematic patterns during sagittal flexion movements. They identified four subgroups which distinctly differ in range and speed of motion, muscle relaxation, and lumbo-pelvic contribution to movement. These findings demonstrated the feasibility of subgrouping without pre-classification based on observation or subject history and highlighted the heterogeneity of lumbo-pelvic kinematics within an LBP sample. They also support the notion of improving treatment efficacy by tailoring to kinematic deficits as opposed to subjective pain experiences or observations.

It is of note that sagittal flexion was the only evaluated movement, with no inclusion of other single-plane or multi-plane movements. As such, functional movement-related classifications described by Hemming et al. [5] were not incorporated. Similarly, O’Sullivan [7] described specific classifications which manifest only during functional tasks. However, the study was limited to an Australian population, and as discussed by the authors, results have not been verified in an independent sample.

Matheve et al. [8] assessed the effectiveness of sensor-based postural feedback in modifying lumbo-pelvic motor control in Belgian patients with chronic LBP, and healthy controls. The intervention comprised of two movement control tasks conducted in a single exercise session (lifting task & waiter’s bow). The authors concluded that postural feedback was effective in improving lumbo-pelvic control. Tsang et al. [9] evaluated the difference in lumbo-pelvic movement patterns between healthy and low back pain subjects using a 3-dimensional inertial sensor system (3D MyoMotion). Seventeen males with low back pain and eighteen males without were instructed to bend forward at five selected speeds while wearing the sensors. The study evidenced the system’s ability to track movement patterns and highlighted that subjects with low back pain adapt to carry out the same motion as those who are asymptomatic.

Other studies of posture and back movements combined inertial sensors with electromyography (EMG) sensors. In a preliminary study of the mDurance device, Banos et al. [10] conducted trunk endurance assessments on subjects currently undergoing physical therapy. The device was effectively able to manage movement data recorded during the tests. In a cross-sectional study by Laird et al. [11] used the combined motion and surface electromyography (sEMG) capabilities of ViMove and observed diminished range of motion in the trunk, lumbar, and pelvis along with slowed overall movement in those with low back pain. They also noted significant differences of flexion-relaxation between LBP and healthy controls as assessed through sEMG. However, the study was limited to evaluation of flexion and seated postures, and only examined univariate relationships.

To better understand and characterize movement patterns both in populations with and without LBP in a broader set of movements, dorsaVi established the Back Pain and Movement (B-PAM) Registry. The purpose of B-PAM is to provide baseline, follow-up, and normative data pertaining to single-plane and dynamic movements of normal controls as well as those with LBP, as assessed by ViMove, in a U.S. sample population. ViMove is capable of continuously measuring 3-dimensional lumbosacral movements and sEMG for up to 24 h. This system has been validated against gold standards for motion analysis including Optotrak and Vicon motion capture systems where it demonstrated clinically acceptable agreement with these motion laboratory-based systems [12]. The movement consistency of ViMove between tests on the same and different days has also been evaluated for flexion, extension, and lateral flexion [13]. Intraclass correlations of r = .88 (range .80 to .98) and r = .85 (range .69 to .97) were observed respectively indicating good to excellent agreement. ViMove has received FDA 510(k) clearance and is commercially available.

By extending on previous research which only focused on certain movements, and by additionally evaluating sEMG, B-PAM seeks to provide an extensive repository of data for use in defining assessment and treatment algorithms while evaluating performance of specific movements. The B-PAM data is intended to benefit and support interests of patients, practices, hospitals, clinicians, regulatory bodies, payers and industry by streamlining the clinical surveillance process and facilitating leading edge performance assessment while also gathering baseline data without intrusion into clinical pathways.

The registry seeks to address the following questions in a U.S. population sample:Are there differences in range of movement and kinematics (e.g. speed and pelvic/lumbar contribution of movement) between patients with LBP and subjects without LBP?Are there differences in secondary outcomes (leg/back pain, depression, health-related quality of life) between those with LBP and without LBP?Are there identifiable lumbo-kinematic patterns and muscle-activity associated with LBP patients during single-plane and dynamic movement?Are there associations between the demographic and clinical characteristics (e.g. age, gender, level of back pain) and kinematic outcomes in LBP patients?

## Methods/design

This is an ongoing, non-randomized, prospective post-market registry consisting of two groups: patients with LBP, and age and sex-matched controls without LBP. We will recruit a total of 132 subjects in each group. B-PAM has a flexible design to allow new dorsaVi products to be added to the registry following their market release. Data collection will take place in two phases: (1) baseline assessment of LBP patients and matched controls; (2) assessment of LBP patients at 6 and 12-months follow up.

Reporting and data analysis of the B-PAM registry will be undertaken in accord with The Strengthening the Reporting of Observational Studies in Epidemiology (STROBE) guidelines for reporting observational studies [14].

### Site selection

Sites participating in B-PAM will initially be two clinical centers in Washington DC, USA (International Spine Pain & Performance Center and Synergy Manual Physical Therapy).

### Subject selection

Subjects with LBP will be included if they fulfil the following criteria:Subject or legally authorized representative provides written authorization and/or consent per institution and geographical requirementsSubject with a predominant complaint of LBP of any duration, with a minimum daily pain average visual analogue score (VAS) ≥ 30/100Subject is intended to be assessed with the eligible product

Exclusions to enrollment are:Unable to be available for study follow-upsExclusion criteria required by local lawMovement assessment is contraindicated for any reason.Currently enrolled in or plans to enroll in any concurrent drug and/or device study that may confound resultsBody mass index ≥35 kg/m^2^

Controls will be recruited using study advertisement flyers posted on campus at the George Washington University, local gymnasiums, recreational centers, via word of mouth, and email list servers associated with educational programs within The George Washington University School of Medicine and Health Sciences. Subjects will be screened by phone for the presence or history of LBP (no current LBP and no history of LBP lasting longer than 3 months in the past 12 months) as well as other exclusion criteria listed above. Controls will be age and sex-matched with LBP patients on a one-to-one basis.

### Minimization of bias

The following procedures have been incorporated to minimize potential bias:Sites will screen and consecutively enroll all subjects who undergo assessment.The Principal Investigator will be blinded to results of assessment.Sites must meet pre-defined criteria to be selected to participate.Standard operating procedures for data collection will be employed across study sites with a single common database for all sites.

### Sample size

Detection of a ‘moderate’ effect size (i.e. Cohen’s effect size of ≥0.40 in range of movement and other outcomes) between LBP and controls requires 132 individuals per group at 90% power and alpha of 5% (estimated using STATA’s sampsi command) [15].

Based on this sample size and using data in individuals with no back pain reported by Laird (Monash University, Research Project Report No: cf11/0748–2,011,000,372), Table 1 shows the predicted minimum mean difference that could be detected between back pain and control groups. The magnitude of these predicted between-group differences in range of movement appear to be fairly consistent with those reported in the meta-analysis conducted by Laird et al., evaluating previously published studies comparing LBP and control populations [3].

**Table 1 Tab1:** Range of motion and predicted minimum mean differences between back pain and control groups

ROM outcome	Non-back pain group Observed Mean (SD)	Predicted minimum mean difference between control and back pain group
Lordosis		
30–39 years	-30 (6.9)	± 2.76
40–49 years	−32 (10.1)	± 4.04
50–65 years	− 36 (12.2)	± 4.88
Standing flexion		
30–39 years	46 (11)	± 4.4
40–49 years	48 (6)	± 2.4
50–65 years	46 (9)	± 3.6
Standing extension		
30–39 years	−26 (10)	± 4.0
40–49 years	−18 (11)	± 4.4
50–65 years	−17 (14)	± 5.6

We have also estimated the impact sample size of 132 back pain individuals in terms of achieving our second research objective of assessing the subject demographic and clinical characteristics associated with range of movement. Based on the rule of thumb of 10 observations needed per covariate (or predictor) [16], 32 individuals with back pain would allow for a multivariable regression including up to 13 covariates. 132 subjects would also allow detection of an increase in the f2 of multivariable model with 9 covariates from 50 to 55% with the inclusion in the model of one additional covariate at 90% power and 5% alpha (using STATA’s powerreg command) [17].

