#### Association between demographic and clinical characteristics and range of movement outcomes in LBP subjects

Pearson correlation coefficients will be used to assess the univariable association between range of movement and various back pain subject characteristics. Multivariable associations will also be assessed using multivariable Pearson correlation coefficients and multivariate linear regression analysis. In determining multivariable models, collinearity between potential variables will first be assessed and variables where high collinearity will be excluded.

The focus on all data analyses will be on those registry participants with complete data. However, we will report rates and reasons for missing data and, where appropriate, consider imputation of missing cases using appropriate statistical methods.

All inferential analysis results will be reported as mean differences and 95% confidence intervals. We will report *P*-values to three decimal places with P-values less than 0.001 reported as *p* < 0.001. All statistical tests will be performed using two-sided tests at the 0.05 level of significance. No formal adjustment of the level of significance for testing will occur, but P-values will be interpreted accordingly, considering the multiple testing outcomes. An analysis will be undertaken at the end of the phase I, upon completion of enrolment of the age and sex-matched cohorts, prior to proceeding with enrolment of phase II of the registry.

All analyses will be undertaken using STATA version 14 [17].

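### The regression power statement is false as written on the f2 scale, does not reproduce 90% on the R² scale, and the covariate rule is applied to 32 patients instead of 132

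*Protocol article*

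**What the plan says.** The protocol article, Sample size, first derives the group size from the two-group comparison: a standardised difference of 0.40 "requires 132 individuals per group at 90% power and alpha of 5"%.

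It then asks what that fixed number can do for the analysis of patient characteristics associated with range of movement: "We have also estimated the impact sample size of 132 back pain individuals". Two supports follow.

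- A covariate rule: "Based on the rule of thumb of 10 observations needed per covariate (or predictor"), from which it concludes that "32 individuals with back pain would allow for a multivariable regression including up to 13 covariates".
- A power statement: "132 subjects would also allow detection of an increase in the f2 of multivariable model with 9 covariates from 50 to 55" per cent. The gain is attributed to a single extra predictor. The power claimed for it is 90%, the alpha is 5%, and the source is named as Stata's powerreg.

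The statistical analysis text sets the test level: "All statistical tests will be performed using two-sided tests at the 0.05 level of significance".

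**The concern.** f2 and R² are different quantities. For a whole model f2 = R²/(1 − R²), so 50% on one scale is not 50% on the other, and an increment of five points means something quite different on each. The power attached to 132 patients depends heavily on which was meant, and the literal wording names f2.

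The covariate sentence does not follow from its own rule: 13 covariates at 10 observations each need 130 patients, not 32.

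These two sentences are the only sample-size support given for the association objective. As they stand, a reader cannot tell what increment in explained variation the registry can detect. The literal figure would promise 90% power where there is little better than an even chance.

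**Working it through.** **Inputs (protocol article).** From Sample size: N = 132 patients; one covariate added to nine, so 10 in the full model; power 90%; alpha 5%; 10 observations per covariate. From the statistical analysis text: two-sided tests at 0.05. An F test with 1 numerator degree of freedom is equivalent to a two-sided t test, so no adjustment is needed.

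**1. The plan's main figure, as a check.** n per group = 2(1.960 + 1.282)²/0.40² = 131.3, rounded up to 132; power at 132 is 90.1% (normal approximation). The two-group figure reproduces.

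**2. Method for the regression.** Partial f2 = (R²_full − R²_reduced)/(1 − R²_full). The test is a noncentral F with df1 = number of covariates tested, df2 = N − 10 − 1 = 121 and noncentrality λ = N × partial f2. Some software multiplies by df1 + df2 + 1 or by df2 instead of N; ranges over these conventions are shown.

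**3. f2 as written, 0.50 to 0.55.**
- R² reduced = 0.50/1.50 = 0.3333; R² full = 0.55/1.55 = 0.3548.
- Partial f2 = 0.0215/0.6452 = 0.0333; λ = 132 × 0.0333 = 4.40.
- Power at 132 is 54.8% (51 to 55% over the conventions). N for 90% is 318 (318 to 329).

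**4. R² from 0.50 to 0.55.**
- Partial f2 = 0.05/0.45 = 0.1111; λ = 132 × 0.1111 = 14.67.
- Power at 132 is 96.7% (95 to 97%). N for 90% is 97 (97 to 108).

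**5. What 132 patients can detect at 90% power with one added covariate.** R² from 0.50 to about 0.5375 (partial f2 = 0.0375/0.4625 = 0.0811, power 90.1%), or f2 from 0.50 to about 0.62.

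**6. Which inputs would give 132?** With R² from 0.50 to 0.55 and λ = N × partial f2, varying the number of covariates tested:

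| Covariates tested | Power at 132 | N for 90% |
|---|---|---|
| 1 | 96.7% | 97 |
| 2 | 93.3% | 118 |
| 3 | 90.06% | 132 |
| 4 | 86.9% | 144 |

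Three tested covariates return 132 exactly, and they still do if the full model has 12 predictors (nine plus three) instead of 10. The match depends on λ = N × partial f2; the other conventions give somewhat larger numbers.

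**7. Covariate rule.** 32/10 = 3.2, so 3 covariates. 132/10 = 13.2, so 13 covariates.

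**The case against.** The best defence is that the power sentence claims sufficiency, not an exact requirement. The 132 comes from the two-group comparison, and the regression paragraph only says what that number would allow. A percentage belonging to a model is natural for explained variance and odd for f2, which is an unbounded ratio. Read as R², 132 patients exceed the 97 needed, so the claim is true. The 32 is an evident dropped digit, because the same paragraph opens with 132 and 13 covariates fit only 132.

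Most of this stands, and it limits the point in three ways.

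- A reader might infer that the power claim is wrong whichever measure was meant. The document does not support that: on R² it is conservative, and surplus power is not an error.
- A reader might infer from the 55% that the registry is underpowered for this objective. That follows only on the literal f2 reading, which is the less plausible one.
- A reader might infer that the regression is planned on 32 patients. The surrounding sentences, both of which name 132, rule that out.

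What the defence does not remove is that the text names f2, for which the figure fails; that 90% is not what the stated inputs give on either scale; and that 32 contradicts the rule it is used with.

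**Conclusion.** The point holds as a correction to two stated figures. As written, on f2, the power is about 55% and not 90%, a gap of about 35 points, and 90% would need about 318 patients (318/132 = 2.4 times as many). On R², the likelier intention, power is about 97%: the claim is safe, but 90% is not reproduced for one added covariate. The 32 should be 132.

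That R² was intended, and that the number of added covariates may also be misstated, are inferences. The first rests on the percentage wording and the second on three covariates reproducing 132; the document states neither. The power figures assume the usual fixed-predictor F test for an R² increment, and no convention for the noncentrality parameter closes the gap on either scale. The primary sample size, recruitment and planned models are not affected.

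**What to change.** Recheck the original powerreg run, then rewrite two sentences.

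- Name the effect measure (R², if that was meant) and the number of covariates tested, and give the power that matches. For one covariate added on R²: about 97% power for 0.50 to 0.55, or 90% power for 0.50 to about 0.5375. For three added covariates on R²: 90% power for 0.50 to 0.55. If f2 really was intended, state about 55% power for 0.50 to 0.55, or 90% power for 0.50 to about 0.62.
- Change 32 to 132 in the covariate sentence.

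The choice among these should come from the run itself and not from working back to 132. The cost is two corrected sentences; design, recruitment and analysis do not change.

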### Ethical approval

Prior to enrolling any subjects into B-PAM, sites must fulfil all local law and regulatory requirements. The term Ethics Board will be used to define the Institutional Review Board (IRB), Medical Ethics Committee (MEC), Research Ethics Board (REB) or Human Research Ethics Committee (HREC). Participation readiness includes but is not limited to:Ethics Board approval or a written statement by the Ethics Board Chairperson stating that approval is not required.Approval of the Informed Consent (CF) or Data Release Form (DRF) by the Ethics Board and/or sponsor (if required).A legally executed Agreement.Insurance certificates (as required by geography).Applicable Regulatory Approval (as required by geography).Documented training; signed and dated.

Subjects can exit from B-PAM if: they choose to withdraw, reach end of their follow-up period, the investigator deems withdrawal is necessary (e.g. medically justified, failure of subject to maintain adequate registry compliance, or if the subject is no longer available for follow-up.

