### Measurements

General data collection procedures and the scope and timing of demographic data outcome collection are summarized in Tables 2 and 3 respectively.

**Table 2 Tab2:** Summary of data collection

	Enrollment	Baseline/Assessment	Follow-Up	Exit
CF or DRF Signed and Dated	X	X		
Subject Demographics	X	X	X	X
Outcome Measures	X	X	X	X
Medical History	X			
Assessment Details	X	X	X	
Patient Status	X	X	X	X
Events	X	X	X	X
Protocol Deviations	X	X	X	X

**Table 3 Tab3:** Summary of collected demographic and outcome data

Demographic measures	LBP Patients	Controls
Age	X	X
Gender	X	X
Pain episode duration (weeks)	X	X
Body Mass Index (BMI)	X	X
Employment (working vs not working)	X	X
Marital Status	X	X
Co-morbidities (categories)	X	X
Co-interventions - current medications (categories)	X	X
Co-interventions - (hospital admissions, doctor or other clinician visits, imaging, other diagnostic tests,	X	X
Patient outcomes		
LBP diagnosis (ICD-10) - clinician	X	
LBP – movement pattern classification (clinician)	X	
LBP – Movement Classifier	X	
QVAS - back	X	X
QVAS - leg	X	X
Oswestry Disability Index (ODI)	X	
START-Keele	X	
Fear Avoidance Behavior Questionnaire (FABQ)	X	
EQ-5D	X	X
Depression Anxiety Stress Survey 21 (DASS-21)	X	X
Patient perception of movement contribution to pain - single item	X	
Movement outcomes		
ViMove standard assessment (includes range of motion, speed, and timing of movement as described in “Measurements”)	X	X
30 s sit-to-stand test	X	X
40 m walk test	X	X

The dorsaVi ViMove system consists of two wireless tri-axial inertial measurement sensors containing accelerometers, gyroscopes, and magnetometers. These allow evaluation of movement in all three anatomical planes. Additionally, two wireless, bipolar, ViMove surface electromyography (sEMG) sensors will be placed on the subject’s low back via a disposable adhesive safe for human-use at standardized locations based on anatomy and subject height. Once these sensors are placed (at approximately the L3-vertebrae), the subject will be asked to move through a sequence of assessments (see Table 4).

**Table 4 Tab4:** ViMove (dorsaVi) Assessment

Posture / Movement performed by subject:	Instructions to the Subject
Standing – ‘normal’ posture (calibration)	● Warm up – walk at comfortable pace for 20 s. ● Stop and reach towards the ceiling as high as you can. ● Stand with feet hip distance apart. ● Look straight ahead. ● Now we are going to measure your posture ● Stand still whilst I count to 5.

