LBP patients and non-LBP controls will be assessed at enrolment (baseline). LBP patients will then then be followed up at 6 and 12 months (see Fig. 1).

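### The exit rule lets the investigator end all registry follow-up on medical or compliance grounds, so the 6- and 12-month change analyses and event capture in LBP patients may lose patients selectively

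*Protocol article*

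**What the plan says.** The exit rule is a single sentence under Ethical approval in the protocol article. It begins "Subjects can exit from B-PAM if: they choose to withdraw, reach end of their follow-up period" and then adds the case where "the investigator deems withdrawal is necessary (e.g. medically justified, failure of subject to maintain adequate registry compliance". Loss of availability for follow-up is named separately. The thing exited is the registry, not a particular procedure.

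Methods/design describes an observational registry whose second phase is "assessment of LBP patients at 6 and 12-months follow up"; controls are seen at baseline only. Table 2 has an Exit column, and its outcome row reads "Outcome Measures X X X X". Patient Status and Events are also marked at Exit. Table 3 lists the self-reported outcomes, among them back and leg pain, EQ-5D and, for LBP patients only, the "Oswestry Disability Index (ODI)". It lists the movement tests in a separate block.

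Statistical analysis plans within-group comparisons of follow-up with baseline and centres all analyses on participants with complete data. Rates and reasons for missing data are to be reported, and imputation is only to be considered.

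**The concern.** In a registry that assigns no treatment, there is no study treatment to withdraw. What may become unsuitable or be missed is the movement session. Pain, disability and quality-of-life questionnaires, co-interventions and events can be collected without it. The rule nonetheless ties them together: on medical or compliance grounds, a patient who has not withdrawn and can still be reached may leave all follow-up.

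Such losses come from a decision, not from the patient's absence, so they are avoidable. If they fall more often on patients who are doing badly, mean change in those who remain looks better than it is, and later events go unrecorded. Reporting the reasons for missing data does not recover data that were never sought.

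**Working it through.** **1. Which data are at risk.** Exit can be decided on medical or compliance grounds (Ethical approval). One set of outcomes, status and events is scheduled at Exit (Table 2). No collection after Exit is described. The loss is therefore of data after exit. As an illustration, a patient exited at month 4 would have an exit record but neither scheduled follow-up visit, and 12 − 4 = 8 months of events would be uncollected.

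**2. Which analyses are exposed.** The Abstract states: "The primary outcome measure will be differences in movement patterns between those with LBP and those without LBP". Controls are measured only at baseline, and a phase I analysis is planned before phase II begins, so later exits do not touch the baseline comparison. Exposed are the within-LBP changes at 6 and 12 months and the event record.

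**3. The plan's own figure.** Inputs from Sample size and Statistical analysis: standardized difference 0.40, two-sided 5% level, 90% power.

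n per group = 2 × (1.960 + 1.282)² / 0.40² = 131.4, rounded up to 132. Power at 132 is 90.1%. The stated 132 is reproduced.

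**4. Size of the possible bias.** The documents give no exit rate, so w = 5%, 10% and 20% are assumptions. Let change in LBP patients be normal with true mean 0 and SD 1, higher meaning worse. φ is the standard normal density.

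*Moderate case: exit twice as likely in the worse half.* The exit probabilities are 4w/3 in the worse half and 2w/3 in the better half. The half means are ±2φ(0) = ±0.798. The mean among those retained is −0.5 × 0.798 × (2w/3) / (1 − w).

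*Extreme case: only the worst fraction w exits.* The mean among those retained is −φ(c) / (1 − w), where c is the 1 − w quantile.

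For w = 10%:
- moderate: 0.399 × 0.0667 / 0.90 = 0.030
- extreme: 0.1755 / 0.90 = 0.195

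| Assumed exit | LBP patients left of 132 | Bias, moderate (SD) | Bias, extreme (SD) | SE of mean change, 1/√n (SD) |
|---|---|---|---|---|
| 5% | 125 | 0.01 | 0.11 | 0.089 |
| 10% | 119 | 0.03 | 0.19 | 0.092 |
| 20% | 106 | 0.07 | 0.35 | 0.097 |

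All biases are towards apparent improvement. In the moderate case they stay below the standard error of the mean change; in the extreme case they exceed it. The 0.40 in Sample size is an LBP-versus-control effect and is not a yardstick for within-patient change.

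**The case against.** The strongest reply has four parts.

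**The rule is permissive and an exit record is scheduled.** This stands. A reader might infer that removed patients lose all event, pain and disability data. Table 2 does not support that, because Outcome Measures, Patient Status and Events are marked at Exit. A reader might also infer that a patient who becomes unfit for testing must be either re-tested or removed. The text says only that subjects can exit; nothing makes a missed movement session a reason for removal, and the analysis section expects incomplete records.

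**Selection by worsening is not stated.** This also stands. Medical grounds permit it, but the article says nothing of how often exits would occur or in which direction. Poor compliance has no stated direction.

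**The entry criteria do not conflict with the repeat sessions.** It is tempting to see a contradiction because contraindication to movement assessment is only an enrolment exclusion and "Medical History" is marked only at Enrollment, while "LBP patients will then then be followed up at 6 and 12 months". The documents do not support this. Eligibility naturally applies at entry, and Table 2 collects demographics, status and events at follow-up. In Table 3 the demographic block includes co-morbidities and hospital admissions.

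**A condensed article may leave partial follow-up to the full protocol.** That protocol is not shown and may contain such a provision; if so, the sponsor need only point to it. But the point does not rest on silence alone. The article states a rule that ends registry participation on these grounds, and that rule as worded is what needs qualifying.

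**Conclusion.** The point holds in limited form. The stated rule allows avoidable and possibly selective loss of follow-up among LBP patients who have not withdrawn and can still be reached, and the complete-data focus carries that loss into the within-LBP change results. Events after exit would also be missed.

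The size is unknown because no exit rate is given. For assumed exits of 5% to 20%, the bias in mean change is about 0.01 to 0.07 SD under moderate selection and 0.11 to 0.35 SD if only the worst exit. Both sets rest on a normal distribution of change, on the assumed rates, and on exits being related to outcome. If exits are unrelated to outcome, precision is lost but there is no bias.

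A reader might infer that the registry's main finding is threatened. It is not: the baseline LBP-control comparison is unaffected.

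**What to change.** Amend the exit sentence under Ethical approval as a data-collection rule. Inadequate compliance, or an investigator's decision to stop assessments, would not by itself end data collection. For patients who have not withdrawn consent and remain reachable, the questionnaires, co-interventions and events in Tables 2 and 3 would continue to be sought at 6 and 12 months. The reason for any stopped assessment would be recorded. A note to Table 2 could make clear that such patients stay under the Follow-Up column.

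This sets no clinical criterion for who is re-tested; that remains with the clinicians.

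The cost is one amended sentence and a table note. The drawback is some follow-up records with questionnaires but no movement data. The registry is ongoing, so the change is worth making early: follow-up that was not collected generally cannot be fully recovered later.
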